### Distress in children

The term ‘distress’ refers to a multifactorial unpleasant emotional experience that can be described as a combination of fear, anxiety and pain.^21^ The relationships between these factors are complex, and the experience of distress is based on interactions between ‘genetically linked behaviour patterns, temperamental predispositions, normal developmental fears, parental psychopathology and discrete learning experiences’.^22^ Distress in this study is defined as an experiential response and sensation of the mind associated with negative emotions that appear when a situation is fearful or impossible to manage from the perspective of the child. Distress can be a consequence of insufficient symptom relief, and self-reported distress is a global assessment that reflects the child’s experience of the success of symptom relief. It is important to evaluate the distress in children undergoing cancer treatment and to find strategies for the measurements of symptoms/emotions that are reliable and valid for this purpose. It is known that acute stress activates the hypothalamic–pituitary–adrenal axis and the sympathetic nervous system as well as the hypothalamic–pituitary–gonadal axis.^23–25^ For example, plasma cortisol concentration is an established stress (energy mobilisation) indicator that is known to react within minutes after the onset of stress exposure. Estradiol is on the other hand an anabolic hormone, which protects against adverse effects of stress.

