## Methods and analysis

### Study design

The Medical Research Council’s key principles and actions for development and evaluation of complex interventions^29 30^ guided the intervention development and the research design. In a hybrid design, both the effects of the intervention and the implementation process will be evaluated.^31^ Relevant care situations are selected^32^ where highly standardised care procedures are used and where there is a range of different situations where children struggle with symptoms. To facilitate the effect evaluation, the children will participate in a crossover design study where they are their own controls (figure 1). The study design follows the SPENT 2019 checklist for clinical trials.^33^

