**Figure 1 F1:**
[figure not shown]
The cross-over design with two study groups will participate in two phases as related to the Nordic and European study protocols in Sweden for treatment of children with high-dose methotrexate. All methotrexate treatment sessions take a similar amount of time for the child. The intervals between each of the methotrexate treatments will be controlled by each child’s treatment plan and may vary between 3 and 6 weeks. NRS, numeric rating scale; PicPecc, pictorial support in person-centred care for children.

The development of the PicPecc tool follows established guidelines^34^ and was based on the theoretical framework of person-centred care,^4^ on published systematic reviews^9^ and on systematic reviews conducted within the project on assessment tools for nausea,^35^ and anxiety.^36^ Children with cancer, their legal guardians and healthcare professionals have been involved throughout the development process. The study protocol outlined here pertains to the evaluation and implementation phases.

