### Randomisation

The participants will be allocated codes in a consecutive order; the code is randomly assigned to either the intervention phase (B) or control phase (A). Participating cancer units will be given the solution to the randomisation code once the codes have been allocated to the participants. The participants will only have access to the PicPecc tool during the intervention phase. There will be a period of at least 2 weeks between the end of the first intervention period and the start of the next methotrexate treatment. This provides an adequate washout period between the intervention (B) and the control phase (A) for any behaviour change to revert to previous patterns. Following the transtheoretical model,^40^ habitual behaviour change related to health is a process involving a number of stages that takes time to complete successfully, where support for change is removed early in the process the individual will quickly revert to previous habituated behavioural patterns. We are confident, therefore, that the intervention will have no residual effects on the control phase.

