### Measures and materials

#### Impact evaluation

We consider a difference of 15% to be a meaningful difference in score average between T0 and T2 (48 hours); this is represented by a difference of approximately 1.5 units on the NRS (0–10) of distress, when comparing users of the PicPecc tool to control subjects. The estimate of SD is based on unpublished data of 11 to 12-year-old girls’ self-reports.^41^ Based on an expected SD of 2.9 (and a power of 0.8), it is necessary to include at least 32 participants. With a dropout rate of approximately 20%, 20 participants in each group, that is, 40 participants will be included in the study.

In both the control (A) and intervention phases (B), the data collection follows the test period outline in figure 2. Assessment of distress will be made at time points T-1, T0, T1 and T2. T3 is an interview to evaluate the implementation process. Primary outcome is the difference in delta T0 and T2 between control and intervention phases. The time points are linked to the schedule for the methotrexate treatment to avoid extra blood sampling. The time points will also facilitate the evaluation between before and after treatment, with the objective to evaluate differences in symptoms, with and without the PicPecc tool (figure 2).

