### Data analyses plan

#### Effect evaluation

We expect the intervention to be superior to the control in terms of the health outcome assessment (NRS-11). We also expect that there will be a difference between premethotrexate treatment (T1, T0) and methotrexate treatment (T1, T2) in both intervention and control phases. Therefore, we will test the null hypothesis that there will be neither change in any of the measurements between the premethotrexate treatment (T-1, T0) and methotrexate treatment (T1, T2) nor between intervention and control phases. A p value of <0.05 will be considered as statistically significant. Categorical data will be descriptively analysed by frequency distributions and percentages. The paired sample t-test will evaluate the difference between two sets of assessments and effect size.^47^ Data will be analysed with IBM SPSS Statistics V.25 (New York City, USA).

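### The crossover's paired t-test ignores the randomised order; a period-adjusted analysis would guard against a difference between first and second course at almost no cost

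*Protocol article*

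**What the plan says.** Under Study design, "the children will participate in a crossover design study where they are their own controls". The Figure 1 legend adds "The cross-over design with two study groups will participate in two phases", with intervals between courses that "may vary between 3 and 6 weeks". Under Randomisation, participant codes are assigned at random to the control or the intervention phase; no method of balancing the two orders is described. The Impact evaluation section states the allocation target: "With a dropout rate of approximately 20%, 20 participants in each group, that is, 40 participants will be included in the study".

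The primary outcome (Impact evaluation; Figure 2 text) is the change in NRS distress from T0 to T2, compared between the control and intervention phases.

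Under Data analyses plan, Effect evaluation, the test is stated: "The paired sample t-test will evaluate the difference between two sets of assessments and effect size". No period, sequence or order term appears anywhere in the article. The one order-related effect discussed is carry-over, which is dismissed on the strength of the washout: "We are confident, therefore, that the intervention will have no residual effects on the control phase".

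**The concern.** A two-sequence crossover randomises the order so that a difference between first and second period can be separated from the treatment effect. A paired t-test of PicPecc against control pools the two orders and discards that information.

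The washout argument does not cover this. It concerns residual effects of PicPecc, whereas a course effect can arise with no carry-over at all.

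Two things are at stake. With equal sequences, a course effect inflates the variance that the test uses and lowers power. With unequal sequences, part of the course effect stays in the estimated PicPecc effect of that particular trial.

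The scope is limited by the choice of outcome. Because it is a change within each course, a shift in the overall level of distress between courses cancels. Only a shift in the 48-hour change itself matters.

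**Working it through.** **Inputs.** From Impact evaluation: difference 1.5 NRS units, SD 2.9, power 0.8, 32 evaluable children, about 20% dropout, 40 enrolled. From Effect evaluation: p < 0.05 (sidedness not stated) and the paired t-test. Assumed: P, which the article does not give.

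**The plan's own figure.** Take 2.9 as the SD of the within-child difference, two-sided 5%, noncentral t. Power is 0.796 at n = 31 and 0.809 at n = 32, so 32 reproduces. Then 32/0.8 = 40, as stated. A one-sided paired test would give 25 and two independent groups 59 each, so the stated number is that of an unadjusted two-sided paired t-test.

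**Model.** Let E be the PicPecc-minus-control difference in the T0-to-T2 change (benefit: E = -1.5). Let P be the second-minus-first-course shift in that change. The within-child difference, PicPecc minus control, has mean
- E + P in control-first children (AB);
- E - P in PicPecc-first children (BA).

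The overall mean that the paired test uses is therefore E + P × (nAB - nBA)/n. With equal groups the SD it uses grows to roughly √(2.9² + P²): 3.07 at P = 1, 3.27 at P = 1.5, 3.52 at P = 2.

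The adjusted estimate uses the first-minus-second-course difference, whose mean is -E - P in AB and E - P in BA. Half of (BA minus AB) is E, whatever P is. Its standard error is (2.9/2) × √(1/nAB + 1/nBA), with n - 2 degrees of freedom.

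**Equal completers, 16/16** (40,000 simulated trials per setting; last column by calculation):

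| P | Paired power | Paired type I error | Adjusted power | n the paired test needs for 80% |
|---|---|---|---|---|
| 0 | 0.81 | 0.05 | 0.81 | 32 |
| 0.5 | 0.80 | 0.05 | 0.81 | 33 |
| 1 | 0.78 | 0.04 | 0.81 | 35 |
| 1.5 | 0.73 | 0.03 | 0.81 | 40 |
| 2 | 0.67 | 0.02 | 0.81 | 46 |

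The paired estimate stays at -1.50 throughout.

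**Unequal completers, conditional on the split.**
- 18/14: shift P × 4/32 = 0.125P. At P = 1 the estimate is about -1.38 and power 0.70. With the split reversed they are about -1.63 and 0.84. Adjusted power is 0.80.
- 20/12: shift P × 8/32 = 0.25P. At P = 1 the estimate is -1.25, power 0.62, type I error 0.06. At P = 1.5 the estimate is -1.125, power 0.47, type I error 0.07. With the split reversed at P = 1.5 the estimate is -1.875 and apparent power 0.91, because the benefit is overstated. Adjusted power is 0.78 and the estimate is unbiased.

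**How likely is imbalance?** This depends on an allocation method that the article does not describe.
- Under simple randomisation, 32 completers split exactly 16/16 with probability 0.14, differ by 4 or more with probability 0.60, and split 20/12 or worse with probability about 0.22.
- If 20/20 is achieved and 8 of 40 drop out at random, a 20/12 split has probability 2 × C(20,8)/C(40,8) = 0.003. A split wider than 18/14 has probability 2 × [C(20,8) + 20 × C(20,7)]/C(40,8) = 0.044, so about 96% of splits are 18/14 or closer.

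**The case against.** The strongest reply is that the harm is small and hypothetical. Much of it stands.

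- *The article does not predict a course effect.* A reader might infer one from the introduction's account of distress, which includes "parental psychopathology and discrete learning experiences", or from the staff workshops and coaching that run in both phases. The first is a general description of distress and says nothing about successive methotrexate courses. The second acts on wards over calendar time; nothing says that it alters the T0-to-T2 change between one child's two courses. The article also stresses that care in this setting is highly standardised. A course effect is possible, not expected.
- *Material loss needs a large P.* At P = 0.5 power is still 0.80, so it would be wrong to say that the planned power holds only with no course effect. A clear loss starts between about 1 and 1.5 units, and the upper figure equals the whole target effect.
- *The test is not biased in general.* A reader might infer that the design credits a time trend to PicPecc. With equal sequences it does not, and the test is conservative. Averaged over simple randomisation, the expected value of nAB - nBA is zero, the mean estimate stays at 1.50 in size and type I error at about 0.05. The shifts and the 0.07 error apply only given a realised imbalance, and 20/12 is an unfavourable case.
- *Adjustment is not free if it proves unnecessary.* At 20/12 with no course effect it lowers power from 0.81 to 0.78, about what it saves at P = 1 with equal groups.
- *Secondary outcomes.* The article does not say which of them receive the paired test, so a general effect on them is not shown. The Visual CARE Measure is collected only at T2, so a level shift would not cancel there if it were compared in this way.

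What the reply does not remove is that a test is named, that it ignores the randomised order, and that the washout reasoning addresses a different problem.

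**Conclusion.** The point holds as a near-free improvement. The named paired t-test leaves the trial exposed to a difference between courses in the T0-to-T2 change. With equal sequences the cost is power only: 1 to 3 points up to P = 1, about 8 points at P = 1.5 and 14 at P = 2. With unequal sequences the estimate in that trial is shifted by P × (nAB - nBA)/n, in either direction.

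This rests on 32 completers, 2.9 as the SD of the within-child difference net of any course effect, a two-sided 5% test, and an assumed range for P. The reading of 2.9 follows from reproducing the stated 32; the article describes it only as coming from unpublished self-reports. The documents do not support a claim that the planned analysis is biased on average or favours PicPecc, and the stated sample size is arithmetically right for the test chosen.

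**What to change.** For the comparison between phases, replace the paired t-test with a period-adjusted crossover analysis. Take each child's first-course minus second-course difference in the T0-to-T2 change, compare the control-first and PicPecc-first groups with a two-sample t-test, and halve the difference. Alternatively, fit a linear mixed model with phase, course and a random child effect. For complete pairs in balanced data the two give the same result; the mixed model can also use children with only one course, which matters with about 20% dropout, so the plan should say which is primary. Report the phase effect in NRS units with its 95% CI. Use the same analysis for any other continuous outcome compared between phases.

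The cost is one sentence and one degree of freedom. The order is already fixed by the randomisation, so no new data are needed. With df = 30 at 16/16, power is 0.808 against 0.809, and the required number stays at 32 (40 with dropout). If there is no course effect and the completers split 20/12, power falls from 0.81 to about 0.78.

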### Process evaluation

The qualitative data analysis will be driven by interpretive description methodology, and the analysis will follow a mixed-methods research design, that is, a convergent design, with concurrent timing where qualitative and quantitative data are independent of each other. The goal is to disclose experiential and contextually shaped knowledge.^48^ The qualitative data will be interpreted, and the analysis will lead to the identification of a set of themes, which describe the participant’s experience of using the tool. The quantitative data about the frequencies of the participants’ use of the PicPecc tool will be analysed with descriptive statistics, which will then be integrated with the qualitative analysis to facilitate a deeper understanding of how the participants use the PicPecc tool. Finally, an interpretation will be conducted between qualitative and quantitative data.^49^

### Patient and public involvement

Children with cancer, legal guardians and their healthcare professionals have been involved in the development of the PicPecc tool.^34^ Healthcare professionals have been involved in the development of the hybrid design, in order to optimise the feasibility of the study.

### Data monitoring committee

The study will have an external expert panel that will be responsible for checking the quality of the data in the study. The expert panel will also evaluate ethical issues that emerge during the study period.

### Ethics and dissemination

#### Ethics

Ethical approval was obtained from the Swedish Ethical Review Authority (ref 2019-02392; 2020-02601; 2020-06226) for the planned studies. Children are a vulnerable group since adults have a power relationship with the child, the child with cancer is in a difficult life situation, and the child is expected to share personal stories. All data collection is carried out during hospital treatment, and all ordinary management and safety mechanisms are in place. If complications occur in conjunction with the intervention, these are reported at the usual clinical rounds and will be managed according to the ordinary routines.

The children and their legal guardians will be informed about the purpose of the study. The information to participants states that all participation is voluntary and will not adversely affect the child's healthcare, and that it is possible to withdraw consent without explanation or any negative consequences on their treatment and care. All data will be kept confidential, and it is only the research group that has access to the data. The results will not reveal the identity of the participants. Research with children, legal guardians and healthcare professionals requires an ethics committee approval, written consent from the child and the legal guardian and verbal assent from children unable to read.

### Dissemination

Research findings will be presented at international cancer and paediatric conferences, published in scientific journals and publications for children with cancer and their legal guardians. The results will also be available for professional training purposes.
